In Phase 1 and extending into Phase 2 we will examine Questions 1 and 2. We will use data from a pre-intervention period and Phase 1 to develop and then deliver performance feedback on agreed quality indicators in Phase 2 and validate prognostic models for mortality (addressing Question 4) that can be used in future risk adjusted analyses of programme effects on neonatal outcomes. Across the phases of the intervention we will roll out the job aides, audit tools and communications training and link this with facilitative supervision, mentorship and peer learning with the aim of improving day-to-day clinical NBU care. Our aim is to intensify the focus on mortality reduction in Phase 3 using continued feedback and sharing stories of effective change across the MPN and with senior national level stakeholders. This will provide momentum and encouragement to key individuals at all organisational levels to strengthen change efforts. Data will be collected as the intervention matures through Phases 1, 2 and 3 to examine the evolution of the MPN and its effects (tackling specific Questions 3, 5 and 6) and explore how performance measurement might be integrated into the national health information system (addressing specific Question 7). Data on changes in quality indicators and mortality from across the pre-intervention period and Phases 1 to 3 together with qualitative data from across sub-studies will be employed in the Realistic Evaluation. Further information on the proposed conduct of sub-studies is provided in
Table 2.

**Table 2. T2:** Specific questions - sub-study designs and methods.

Study design and methodology	Study site; study populations; sampling procedures; and data collection procedures
***1. Does co-design of job aides and communications skills training support improve adoption of innovations and the quality of*** ***medical and nursing care***	

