***3. How do important process of care quality indicators and mortality change over the period of MPN participation***	
Building on Phase 1 and the earlier establishment of the information system we will track and develop feedback systems on quality of practices such as feed prescribing, monitoring (e.g. assessment with pulse oximetry) and mortality outcomes and progressively use this to focus hospital teams’ attention on their performance in providing quality care and achieving good survival outcomes. We will aim to further drive local learning on how to improve care through online and MPN meetings between hospitals and promote the use of the information from locally conducted neonatal TCR audits that identify factors that can be modified to improve outcomes.	*Study sites:* This work will include all 11 MPN hospitals. *Study* *populations & sampling:* We will examine medical records for all NBU admissions in Phases 1, 2 and 3 and especially those meeting criteria of being a vulnerable baby (either preterm birth (<37 weeks gestation) or low birth weight (<2500g). *Data collection procedure:* All NBU records from which routine de-identified data are **currently being captured** and we will use the quality indicators developed (e.g. on feeding practices and correct antibiotic use) to provide monthly mortality reports and three monthly summary reports on quality of care indicators. We will track the change in aggregate and hospital specific performance and mortality outcomes over time.
***4. What is the optimum approach for risk adjustment of neonatal mortality so that variations in case-mix and case-severity can*** ***be accounted for when evaluating temporal trends in inpatient neonatal mortality***	

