We will build on prior work undertaken in a single Kenyan hospital to develop two candidate prognostic scores for neonatal mortality and **use data already captured** to undertake external validation and improvement of these modelling approaches. The aim will be to develop a prognostic scoring approach that can be applied at individual patient level that enables us to undertake risk adjustment when tracking the long-term trends in survival outcomes in response to the MPN intervention.	*Study sites:* This work will include all 11 MPN hospitals. *Study* *populations & sampling:* We will use **existing data on over 30,000** **NBU** to validate / revise a preferred prognostic model and then use this model to provide risk-adjusted estimates of mortality each month for the 11 sites for a total of 36 months across Phases 1, 2 and 3. These data will enable us to say with greater certainty whether NBU mortality rates are declining over the period of intervention and potentially in which sub-populations.
***5. How do senior doctors and nurses’ social ties influence the performance of frontline staff and evolve within the MPN influenced*** ***by face to face and online interaction***	

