### Quantitative analyses and sample size

Data from across the phases will be used to develop time-series models interrogating the rate of improvement in process indicators and health outcomes over time and as the network intervention progresses. Data will be collected from the national information system (DHIS2) on at least 30 hospitals not in the network over the same time period. These data will provide a frame of reference that can help us interpret whether any changes in intervention hospitals are plausibly related to intervention or linked to wider secular changes in hospital neonatal mortality in Kenya.

Existing pooled data from 11 hospitals we initially plan to work with and for which we have pre-intervention data indicate we can expect denominators of approximately 1200 babies of any weight and 400 low-birthweight (LBW) babies to be admitted to these NBUs per month. Such denominators would allow for specific monthly performance indicators across the network to be estimated with 95% confidence intervals around the most conservative proportion of 50% of ± 5% and ± 3% for LBW and all babies, respectively. These sample sizes are sufficient for detecting meaningful changes in performance and health outcomes to inform our plausibility analysis and later realistic evaluation. For example, in pooled data across sites inpatient mortality at baseline is currently estimated to be 10% +/- 1%. In an end-line period of three months if crude mortality in the same hospitals is 8% or lower, this would likely represent a significant change. Using appropriate, individual risk adjustment in time series analyses will improve the rigour of these analyses. These sample sizes will also be sufficient for detecting clinically important changes in quality of care indicators as we have demonstrated in previous paediatric work
^36,
37,
113^.

A large body of qualitative data will be collected linked to the specific questions we outline above and that enable us to examine elements of the starting programme theory (
Table 2). Data from across all the sub-studies will be analysed using the realist logic of analysis as set out by Pawson and Tilley
^10^. The goal of the data analysis is to further develop the programme theory (

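### The risk-adjusted mortality series is fixed to Phases 1-3 although pre-intervention data are held, so on that series a decline already under way cannot be separated from a change associated with the network

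*Protocol article*

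**What the plan says.** The primary research question names overall risk-adjusted mortality as an outcome. Three parts of the protocol article bear on which months are analysed.

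- **Table 2, question 4** (risk adjustment) is the only place that defines the risk-adjusted series: "risk-adjusted estimates of mortality each month for the 11 sites for a total of 36 months across Phases 1, 2 and 3". Its stated purpose is to show "whether NBU mortality rates are declining over the period of intervention and potentially in which sub-populations".
- **Table 2, question 3** (process indicators and mortality) sets its population as follows: "We will examine medical records for all NBU admissions in Phases 1, 2 and 3".
- **The text under the primary research question** goes wider. For the Realistic Evaluation it will use "Data on changes in quality indicators and mortality from across the pre-intervention period and Phases 1 to 3". It also says of indicator development: "We will use data from a pre-intervention period and Phase 1 to develop and then deliver performance feedback". The same sentence covers validation of the prognostic models.

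**Quantitative analyses and sample size** refers to "Existing pooled data from 11 hospitals we initially plan to work with and for which we have pre-intervention data", so the earlier data are in hand. Its time-series models draw on data across the phases, without saying whether the pre-intervention period counts. That section also plans DHIS2 data on at least 30 non-network hospitals over the same period, to help judge whether a change is plausibly due to the intervention or to wider secular change.

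**The concern.** Phase 1 is formally part of the intervention: the Intervention delivery section describes network building, co-design and work on information and feedback in that phase. A series confined to Phases 1-3 therefore has no month before the network began. It can show that mortality fell. It cannot show whether the fall was already in progress.

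This matters more here than in a randomised design. The protocol argues against randomised controls, so the hospitals' own earlier trend is the main within-hospital comparison available. The synthesis does include pre-intervention mortality, but nothing says that those months will be risk-adjusted. The adjusted outcome named in the primary question may thus be the one without a pre-intervention segment.

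**Working it through.** **1. The plan's own figures (Quantitative analyses and sample size).** Half-width = 1.96 × √(p(1−p)/n).
- p = 50%, n = 400: 4.9 points (stated ±5%).
- p = 50%, n = 1,200: 2.8 points (stated ±3%).
- p = 10%, n = 3,600 (three months): 0.98 points (stated ±1%).
- 10% against 8% with 3,600 in each period: z = 0.02/√(2 × 0.09 × 0.91/3,600) = 2.96, power about 84%.

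All are reproduced. None depends on the window in question.

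**2. What the Phases 1-3 series can detect.** Inputs from the protocol: 1,200 admissions a month, 10% mortality, 36 months (36 × 1,200 = 43,200 admissions). Assumption: independent binomial months, no clustering or autocorrelation.
- Information per month on the log-odds scale: w = 1,200 × 0.10 × 0.90 = 108.
- Spread of n monthly time points, in years²: S(n) = n(n² − 1)/(12 × 144). S(36) = 36 × 1,295/1,728 = 26.98.
- SE(slope) = 1/√(108 × 26.98) = 0.0185 per year, rising to 0.0192 when the weights follow a falling mortality. Call it 0.019.
- Assume a relative fall of 5% a year that predates the network, and no network effect. Weighted regression on the logit gives z = −2.95, so a decline is declared with probability about 0.84. Mortality in the final quarter would be about 0.10 × 0.95^(33/12) = 8.7%.
- At 7% a year the final quarter is 0.10 × 0.93^(33/12) = 8.2%, close to the 8% in the plan's own example.

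The 5% and 7% rates are illustrations; the protocol gives no secular rate.

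**3. What pre-intervention months add.** In a simulation (1,000 runs per setting), mortality fell from 10% to 8% over the 36 months, with the same log-odds slope already running beforehand and no network effect.
- Phases 1-3 only: a significant decline in about 98-99% of runs.
- Segmented model with 6 to 25 pre-intervention months: a significant downward slope change in about 2-3% of runs (nominal 2.5%).

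**4. What it costs in precision.** With level and slope both free to change, the two segments are fitted separately, so SE(slope change) = √[1/(108 × S(pre)) + 1/(108 × S(36))].

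| Pre-intervention months | S(pre) | SE(slope change), per year |
|---|---|---|
| 6 | 0.122 | 0.277 |
| 12 | 0.993 | 0.098 |
| 18 | 3.365 | 0.056 |
| 25 | 9.028 | 0.037 |

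Without a level term the SE would be 0.047 at 18 months and 0.035 at 25, but that model assumes no step at onset.

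Suppose the earlier period is flat and the whole fall from 10% to 8% starts with Phase 1. The slope change is then (logit 0.10 − logit 0.08)/3 = 0.082 per year. In the simulation without a level term, power to detect it is about 8%, 23%, 40%, 59% and 63% with 6, 12, 18, 24 and 25 earlier months. With the level term, Φ(0.0817/SE − 1.96) gives about 31% at 18 months and 60% at 25.

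**5. How many months there may be.** Question 4 cites "existing data on over 30,000" admissions. 30,000/1,200 = 25 network-months. This is only a rough guide, because an unstated part may belong to Phase 1.

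**The case against.** Several points on the other side stand.

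- **There is a planned check on secular change.** A reader might infer from the Phases 1-3 window that the plan as a whole has no way to tell a secular fall from a network effect. That goes too far: the DHIS2 series serves this purpose, and pre-intervention mortality enters the Realistic Evaluation. The protection is partial. The DHIS2 series is not stated to be risk-adjusted and cannot show an earlier trend specific to the 11 hospitals. Table 2, question 7, itself reports considerable weaknesses in DHIS2 neonatal data.
- **Question 4 claims a decline, not a cause.** If mortality really falls 5% a year, calling it declining is correct. The 84% is therefore not a false-positive rate. It is the chance of a finding that could then be read as a network effect.
- **Windows may differ between a sub-study and the synthesis.** A reader might call this a flat contradiction. It is better described as an inconsistency: the article does not say which window governs the risk-adjusted outcome.
- **Phase 1 exposure is low at first**, with co-design in two or three hospitals and wider roll-out near its end. This gives some early contrast, but the plan does not designate those months as a baseline.
- **Model terms can sit in an analysis plan.** They can. The window and the count of months, however, are fixed in this article.

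A reader might also infer that validating the prognostic score partly on Phase 1 data biases the trend. The documents do not show this: a fixed score applied to every month mainly shifts the level of expected deaths, and no size can be derived.

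**Conclusion.** The point holds in a limited form. The article gives different time spans for the mortality analysis. The one series defined for the risk-adjusted outcome leaves out the pre-intervention months that the protocol says it holds. On that series, a decline that predates Phase 1 cannot be separated from a change associated with the network, and 36 months is enough to register a modest one: about 84% for an assumed 5% a year. The DHIS2 comparison and the unadjusted pre-intervention data reduce the exposure without removing it.

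The figures assume independent binomial months of 1,200 admissions at 10% mortality; clustering or autocorrelation would widen every standard error. The unstated length of the pre-intervention period decides how much can be gained. At 18 to 25 months the slope change is estimable with an SE of 0.056 to 0.037 per year; at 6 months it is close to uninformative. No sample-size statement needs correcting on this account.

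**What to change.** Reconcile the text under the primary research question, Table 2 questions 3 and 4, and Quantitative analyses and sample size, so that they state one window.

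1. Start the risk-adjusted monthly series and the time-series models at the first pre-intervention month with usable data, and state how many such months there are. Extend process indicators back only where they were captured.
2. Report the change in level and slope from the pre-intervention trend alongside the trend within Phases 1-3. Allow for phased onset, since the protocol says the intervention is not introduced all at once.
3. Take the DHIS2 reference over the same extended window where available.
4. Optionally, fit the prognostic score on pre-intervention admissions only. This is not shown to matter.

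The cost is rewording, added analysis and a longer DHIS2 extract; the protocol says the pre-intervention data for the 11 hospitals already exist. The downside to state openly is precision: SE 0.056 (18 months) or 0.037 (25 months) per year for the slope change, against 0.019 for a simple trend, and much wider if the earlier period is short. An inconclusive slope change should then be reported as such, not as evidence of no effect.

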***7. How can better performance measurement be integrated into national information systems to sustain improvement***	
We have conducted with the MoH (Informatics Division) a careful appraisal of existing neonatal data collection approaches within the national DHIS2 system revealing considerable weaknesses ^110^. We will draw on prior work ^38^ to use consensus development methods to develop a core set of preferred neonatal quality and outcome indicators for use at national level. We will follow this with use of human centred co-design approaches to improve the process of neonatal data capture and the DHIS2 tools that support it to enable long-term, large scale tracking of neonatal care and outcomes embedded in the national DHIS2.	This work will be conducted at the national level with the Ministry of Health and its Neonatal and Child Health Unit and its Informatics Division. A stakeholder meeting, linking to one of the proposed MPN meetings, will be held to review and suggest revisions to the current information procedures and tools. Draft quality and outcome indicators developed will be refined and agreed with key stakeholders though the Ministry of Health Technical Group of Experts. Based on this process we will revise existing paper tools and online DHIS2 data capture tools employing co-design workshops and ‘walk-throughs’ with health records information officers and clinicians to develop minimal viable products (MVPs) for initial testing. We will progress these MVPs so they can be incorporated into the DHIS2 system and potentially extend this by enabling distributed data capture through mobile applications.

TCR, team based case review; MPN, multi-professional network; NBU, newborn unit; IDI, in-depth interview; MoH, Ministry of Health; MVP, minimal viable product.

### Quantitative analyses and sample size

Data from across the phases will be used to develop time-series models interrogating the rate of improvement in process indicators and health outcomes over time and as the network intervention progresses. Data will be collected from the national information system (DHIS2) on at least 30 hospitals not in the network over the same time period. These data will provide a frame of reference that can help us interpret whether any changes in intervention hospitals are plausibly related to intervention or linked to wider secular changes in hospital neonatal mortality in Kenya.

Existing pooled data from 11 hospitals we initially plan to work with and for which we have pre-intervention data indicate we can expect denominators of approximately 1200 babies of any weight and 400 low-birthweight (LBW) babies to be admitted to these NBUs per month. Such denominators would allow for specific monthly performance indicators across the network to be estimated with 95% confidence intervals around the most conservative proportion of 50% of ± 5% and ± 3% for LBW and all babies, respectively. These sample sizes are sufficient for detecting meaningful changes in performance and health outcomes to inform our plausibility analysis and later realistic evaluation. For example, in pooled data across sites inpatient mortality at baseline is currently estimated to be 10% +/- 1%. In an end-line period of three months if crude mortality in the same hospitals is 8% or lower, this would likely represent a significant change. Using appropriate, individual risk adjustment in time series analyses will improve the rigour of these analyses. These sample sizes will also be sufficient for detecting clinically important changes in quality of care indicators as we have demonstrated in previous paediatric work
^36,
37,
113^.

A large body of qualitative data will be collected linked to the specific questions we outline above and that enable us to examine elements of the starting programme theory (
Table 2). Data from across all the sub-studies will be analysed using the realist logic of analysis as set out by Pawson and Tilley
^10^. The goal of the data analysis is to further develop the programme theory (
Figure 5) so that it will provide more complete explanations for how the MPN intervention results in changes of the process indicators and health outcomes. This analysis will pay careful attention to the changes in behaviour of actors at multiple levels of the health system that are hypothesised to be necessary to effect large scale change and in keeping with recommendations to conduct in-depth, mixed-method case studies
^59^. To further complement this work and provide important contextual data we will collate information on other programmes being implemented in all Kenyan hospitals and those within the MPN that may influence their neonatal care as well as any major changes in national or county government policies. In addition, the team will use reflective team meetings to carefully document actual network activities taking note of any changes that occur during the process of intervention and recording their reflections on the reasons for these. Our analyses will allow us to explore unintended and potentially emergent consequences of the intervention. For example, we can pay particular attention to how Kenya’s response to the COVID-19 pandemic influences the provision of neonatal care in the short and long-term. We will use this process of critical enquiry to advance our programme theory of what worked, why and under what conditions to improve NBU care
^10^. We will present findings in the form of context-mechanism-outcome configurations that will inform our updating of the programme theory which we will use to guide the design of new large-scale improvement programmes.

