**Figure 3. f3:**
[figure not shown]
Anchors in our reflective and iterative process that guided design of the specific Kenyan newborn unit intervention strategy. In this depiction we illustrate the major thematic factors we continuously navigated between as we sought, through an iterative and reflective process involving the authors and multiple team members, to link our understanding of context to potentially feasible intervention strategies aligned with our understanding of theories that offer potential mechanisms through which change is achieved.

Our overall Programme Theory is presented in
Figure 4. It draws generally on the theory and contextual influences outlined above but we use the structure of ‘If, then, because’ statements to propose much more specific requirements that should be achieved, assumptions that can then be examined in subsequent research (
Table 1)
^97^. At its heart is a central Multi-Professional Network. Operationally we aim that this will comprise two to three respected paediatricians (part-time) and a respected senior nurse (full-time) supported by a small team that supports data capture, analysis and timely performance feedback against key measures of the process and outcomes of care for up to 20 hospitals. In each hospital data are captured by abstracting from paper medical records by a single clerical assistant, a process that has previously proven successful
^99^. Electronic records are not used at scale in the Kenyan public sector
^100^.

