Employing a clinical network as an intervention poses a number of specific evaluation challenges. The use of an experimental design that relies on use of randomisation and controls is problematic for a number of reasons. Here we briefly highlight some key issues. First, the unit of intervention is the network itself even if it comprises multiple organisations or facilities. In this sense the direct comparator should be absence of a network, reducing comparison to one intervention and one control observation which would represent a weak experimental design even if such a study was feasible. Some might consider facilities to be the unit of intervention, these then might be randomly allocated to participation in a network or as ‘controls’. We have previously discussed how randomisation may not achieve equivalence or balance in such a situation if only relatively small numbers of complex organisations such as hospitals can be included for reasons of feasibility
^106^. Amongst these is that the list of known and unknown factors (confounders) that may influence a hospital’s response to intervention is potentially very long and time-varying
^106^. For example, in Kenya these may extend from change in political or hospital leadership to localised strikes to distinct differences in disease epidemiology
^107,
108^. More specific to the LMIC context may be lack of data from control settings needed to evaluate intervention effects on quality or outcomes of care
^109,
110^. To gain such data researchers may have to create and embed new data systems which themselves become a form of intervention
^111^. Denying ‘control’ hospitals access to information that may help them improve poses clear ethical challenges. For multiple reasons, therefore, examining the effects of networks might best be conducted using longitudinal study designs without controls based on a programme theory while using both quantitative and qualitative strategies to examine effects linked to a plausibility framework
^112^. These evaluation designs may take the form of ‘in-depth, mixed-method case studies that pay attention to interconnectedness and incorporate an understanding of how systems come together as a whole from different perspectives’
^59^ and it is this form of evaluation we propose would be most useful to determine the effects of our network intervention and how it might produce both intended and unexpected effects.

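### The one external mortality series comes from a different source than the network's, and drift in its capture of deaths could pass for, or hide, a network effect; a like-for-like DHIS2 extract would guard against this cheaply

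*Protocol article*

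**What the plan says.** **Comparison series.** The section Quantitative analyses and sample size states: "Data will be collected from the national information system (DHIS2) on at least 30 hospitals not in the network over the same time period". The series is to serve as a frame of reference for interpreting "whether any changes in intervention hospitals are plausibly related to intervention or linked to wider secular changes in hospital neonatal mortality in Kenya".

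**Network series.** The section on the initial programme theory says: "In each hospital data are captured by abstracting from paper medical records by a single clerical assistant". Table 2, sub-study 4, adds a patient-level prognostic model, to give monthly risk-adjusted mortality for the 11 sites over 36 months.

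**Quality of DHIS2.** Table 2, sub-study 7, reports "a careful appraisal of existing neonatal data collection approaches within the national DHIS2 system revealing considerable weaknesses". It then says "we will revise existing paper tools and online DHIS2 data capture tools employing co-design workshops". Prototypes are to be tested first and then developed for incorporation into DHIS2. No go-live date is given.

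**Design.** The section Evaluation study design argues that "examining the effects of networks might best be conducted using longitudinal study designs without controls", and gives as one reason the possible "lack of data from control settings needed to evaluate intervention effects on quality or outcomes of care".

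**Data quality inside the network.** Under Intervention delivery, Phase 1 includes work with hospitals on the quality of their routine clinical information.

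**The concern.** Without controls, a fall in network mortality may reflect the network or a trend across Kenya. The DHIS2 series is the only external outcome series the article offers for telling these apart. It differs from the network series in source, and no patient-level adjustment is described for it.

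A fixed difference in completeness does little harm if relative trends are compared. The difficulty is a difference that moves. The article gives two reasons why it might: sub-study 7 aims to change how neonatal data enter DHIS2 nationally, and Phase 1 aims to improve information in the network hospitals. If DHIS2 comes to capture deaths more fully, a real secular fall outside the network is understated and the network looks better than it was. If capture worsens, or recording of admissions improves faster than recording of deaths, the error runs the other way. More admissions or better risk adjustment of the network data would not remove it, because it is bias and not imprecision.

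As described, the comparison includes neither DHIS2 data for the 11 network hospitals nor a check of DHIS2 against abstracted records.

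**Working it through.** **1. The plan's own yardstick.** Inputs from Quantitative analyses and sample size: about 1200 admissions a month, of whom 400 are low birthweight; baseline mortality 10% ± 1%; a three-month end-line; 8% or lower as the example of a meaningful result.

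- Monthly half-width at 50%: 1.96 × √(0.25/400) = 4.9 points and 1.96 × √(0.25/1200) = 2.8 points. The stated ±5% and ±3% reproduce.
- Half-width at 10% over three months (3 × 1200 = 3600): 1.96 × √(0.10 × 0.90/3600) = 0.98 points. This agrees with ±1%.
- Comparing 10% with 8% at 3600 babies per period has about 84% power (two-sided 5%, babies treated as independent).

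These figures stand. The change of interest is therefore 2 points, and bias in the secular comparison should be judged against that.

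**2. Model for capture.** Observed DHIS2 mortality = true mortality × (fraction of deaths captured ÷ fraction of admissions captured). I hold admission capture at 100% and take network abstraction as complete. The article gives no DHIS2 capture rate, so every rate below is an assumption.

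**3. Scenario.** True mortality falls from 10% to 8% in all hospitals and the network has no effect. The network series shows 10% to 8%: a change of −2.0 points, a ratio of 0.80. The apparent network effect is the network change minus the DHIS2 change, or the network ratio divided by the DHIS2 ratio.

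| Death capture, start to end | DHIS2 shows | DHIS2 change (points) | Apparent effect (points) | Apparent ratio |
|---|---|---|---|---|
| 80% to 80% | 8.0% to 6.4% | −1.6 | −0.4 | 0.80/0.80 = 1.00 |
| 80% to 90% | 8.0% to 7.2% | −0.8 | −1.2 | 0.80/0.90 = 0.89 |
| 80% to 100% | 8.0% to 8.0% | 0.0 | −2.0 | 0.80/1.00 = 0.80 |
| 90% to 80% | 9.0% to 6.4% | −2.6 | +0.6 | 0.80/0.71 = 1.13 |

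The true effect is nil in every row. Under constant capture the ratio is right and the absolute contrast is off by only 0.4 points. Under drift both are wrong.

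**4. Timing.** The text following the research questions places the exploration of Question 7 alongside the data collection of Phases 1 to 3, so development of the tools overlaps the 36-month series. Whether revised tools would reach the comparison hospitals within that time is not stated.

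**The case against.** The strongest reply is that DHIS2 is a frame of reference in a plausibility analysis, not the control arm of a formal contrast. No network-minus-DHIS2 estimate is planned, and the main mortality analysis is the risk-adjusted trend within the network. The article also collects context on other programmes, policy changes and COVID-19, and it has pre-intervention data. Crude network mortality is available as well, so the adjustment mismatch can be avoided. All of this stands and limits the weight of the point. It does not supply a second external outcome series.

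Three stronger readings are tempting, and the article does not support them.

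- *The study will itself break the comparison series.* A reader might infer this from sub-study 7. The article describes prototypes for initial testing and a later aim of incorporation. It gives no date and no roll-out to the comparison hospitals. A break is possible, not established.
- *DHIS2 is known to miss deaths.* The reported weaknesses concern neonatal data collection in general. Neither under-capture of deaths nor its drift is stated, so the direction of any bias is unknown.
- *An artefact arises even with flat mortality.* With true mortality at 10% throughout, capture rising from 80% to 90% lifts DHIS2 from 8.0% to 9.0%. But the network series then stays at 10%, so there is no network change to interpret. That artefact should not be set against the 10% to 8% example.

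It may also be said that calibration belongs in a fuller protocol. That is fair for detail. The point here is that the comparison as stated, between two sources, has a better and inexpensive alternative.

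**Conclusion.** The point holds as a cheap improvement, not as an error that must be corrected. The only stated external outcome series comes from a different source than the network series, and the article gives reasons why capture could change in either during the study. With assumed rises in DHIS2 death capture from 80% to between 90% and 100%, a shared secular fall of 2 points would yield a spurious network benefit of 1.2 to 2.0 points. A fall in capture from 90% to 80% would yield a spurious 0.6 points against the network. With constant capture the relative comparison is sound.

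These sizes rest on assumed capture rates, complete capture of admissions and complete abstraction in the network. They show what drift could do, not what it will do. The risk-adjusted trend within the network is unaffected; what is weakened is the step from that trend to a statement that it is not secular.

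**What to change.** 1. Extract DHIS2 admissions and deaths for the 11 network hospitals as well, from the pre-intervention period on. Make the secular comparison DHIS2 against DHIS2, crude against crude, over the same months. Keep the abstracted, risk-adjusted series for the within-network analysis.
2. In the 11 hospitals, report each month the ratio of DHIS2 to abstracted deaths, and likewise for admissions, as a check on capture drift. State that this may not carry over fully to non-network hospitals, since the network is itself working on its information.
3. Record by hospital the date on which any revised DHIS2 tool goes live, and either end the comparison series there or model a break at that date. Holding back deployment is a less certain option: the revision is done with the Ministry of Health, and the team, which has no formal authority over health care delivery, may not control the timing.

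The cost is one further extract from a system already being used, some extra analysis, and possibly a shorter comparison series. No new sites and no change to the intervention are needed.
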